#### Inclusion criteria

Adult patients older than 18 years;Lower back pain that is chronic or combined with neurological symptoms of the lower extremities;Single-segment lower lumbar vertebral disease (including lumbar spinal canal stenosis, foraminal stenosis, segmental instability, lumbar disc herniation and painful disc degeneration (back disc)); andInefficacy after strict conservative treatment for more than 6 months.

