#### Sample size calculation

We performed a power analysis to assess the required sample size to show safety with a power (1−b) of 0.8 and α of 0.05. Based on the pre-experiment and related literature,^21^ the proportion of the control group was set to 84.6%, and the proportion of intervention group was set to 95%. We performed a two independent proportions power analysis on PASS (Power Analysis and Sample Size), and the result was 132.

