### Study procedure

A retrospective review of all patients will be conducted by examining their medical records before the operation. The involved segments were identified via a C-arm machine and then marked on the patient’s skin. The patients’ CT images with a thickness less than 1 mm will be exported from the Star PACS image system of the hospital and imported into the Mimics 16.0 to construct 3D images, in which we adjust the threshold depending on the bone density. We regard the two adjacent segments as a functional segmental unit (FSU), such as L2-3, L3-4, L4-5 or L5-S1.

Then, the individual 3D navigation templates will be designed and printed using CATIA software and MeditoolCreate. The detailed steps are as follows: the FSU digital data in the Mimics 16.0 will be saved in STL format and imported into CATIA software. We will establish the optimal screw trajectory, which includes two vertebral pedicle screws trajectories and one contralateral translaminar facet screw trajectory. We will measure three angles of the translaminar facet screw trajectory: α, β and γ; α is the angle between the screw trajectory and the vertical line in the anteroposterior view; β is the angle between the screw trajectory and the upper endplate of the lower vertebra in the lateral view; γ is the angle between the screw trajectory and the midline of the lumbar vertebra in the top view (figure 2). The pedicle screw trajectories will be designed according to method of Roy-Camille.^22^ We will measure two angles, δ and ε, which is the angle between the ideal screw trajectory and the midline of the lumbar vertebra in the top view, respectively (figure 2).

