**Figure 5 F5:**
[figure not shown]
One example of the experiment on conducted 3D printed lumbar model before clinical application to make sure the accurate screw trajectory.

The 3D navigation template will be sterilised and used to guide the screw in further operations on the patients. In experimental group, the dissection of the paraspinal tissue will performed at one side to expose the part of spinous process, laminar and facet joint; the 3D navigation template will be attached to the surface of the above bony construction. Then, the Kirschner wire (K-wire) will be inserted inside the 3D navigation template, and a trajectory for the screw will be fashioned with a cannulated drill; screws will be subsequently introduced. In the control group, multiple X-ray fluoroscopy will be used, and the screw trajectory will be adjusted by intraoperative X-ray fluoroscopy.

After the operation, CT scans of the patients in both groups will be obtained, and the α1, β1, γ1, δ1 and ε1 angles will be measured corresponding to the angles of the optimal screw trajectory in 3D images. The placement and position of the screws will be divided into three types (type I, the screw does not penetrate out of the cortex; type II, the screw partially penetrates out of the cortex, but by less than 2 mm; and type III, the screw penetrates out of the cortex by more than 2 mm).

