### Outcome measure

#### Primary outcomes (table 1)

**Table 1 T1:** The data need to collect through the research

	Baseline	Perioperation	Postoperation				
Assessment	−1 day	Day 0	Day 1	3 months	6 months	12 months	24 months
Eligibility criteria	×						
Recruitment	×						
Informed consent	×						
Randomisation	×						
Baseline demographics	×						
Medical history	×						
X-ray exposure		×					
Wound incision length		×					
Operative time		×					
Blood loss		×					
Complications		×	×	×	×	×	×
Screw angles							
α1			×				
β1			×				
γ1			×				
δ1			×				
ε1			×				
The position of the screws			×				
VAS of back pain	×		×	×	×	×	×
VAS of leg pain	×		×	×	×	×	×
ODI	×		×	×	×	×	×

ODI, Oswestry Disability Index; VAS, visual analogue scale.

Screw angles compared with the optimal screw trajectories in the 3D digital images and the position of the screws.Wound incision length, operative time, intraoperative blood loss, times of X-ray exposure and complications.

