### Statistical analysis

All data will be analysed using SPSS V.19.0 software. The differences in wound incision length, operative time, intraoperative blood loss and angles between the two groups will be analysed using a two independent-sample t-test with an α of 0.05. VAS and ODI scores at preoperation, postoperation, 3 months postoperatively, 6 months postoperatively and 12 months postoperatively will be analysed using a repeated-measures analysis of variance. The times of X-ray exposure and frequency of screw penetration out of the cortex will be compared using the χ^2^ test.

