## Discussion

Translaminar facet screw fixation has been reported as a minimally invasive technique,^11 12 23^ and biomechanical comparisons between facet screw and pedicle screw fixation have revealed biomechanical equivalence between them.^14 15 24^ Unilateral lumbar pedicle screw may be used by some surgeons; however, Sethi *et al*^25^ used in vitro human cadaveric lumbar spines to compare the biomechanical properties of bilateral pedicle screws, unilateral pedicle screws (UPSs), UPSs and translaminar facet screws, and unilateral single pedicle screws and translaminar facet screws (V construct). They found that the UPS construct was the least stable in all loading modes and that the added translaminar facet screw enhanced the stability and stiffness. Similar results were obtained from a finite element analysis study.^26^ The biomechanical study of Luo *et al*^27^ revealed that a significantly larger displacement of the contralateral articular process was recorded in a model with only unilateral pedicle screws, and they reported that the unilateral pedicle screw combined with a contralateral translaminar facet screw had an instant and long-term equivalent biomechanical ability to that of the traditional bilateral pedicle screw (making it an alternative to the bilateral pedicle screw) and could be less invasive while maintaining stable and effective instrumentation.

Current computer-assisted surgery systems can achieve the accurate screw trajectory; however, the cost of computer-assisted surgery systems is considerable, and the manipulation is too complicated,^28^ whereas the accuracy remains dependent on multiple radiations.

Combining 3D reconstruction and 3D rapid printing is a new mode of production, which is applied in many fields because of the advantages of visualisation, plasticity and rapid printing.^29–31^ Moreover, 3D printing templates can help surgeons to achieve accurate screw placement for posterior cervical fixation and scoliosis.^32 33^

In this study, we will compare the 3D navigation template to multiple X-ray fluoroscopy for guiding a unilateral lumbar pedicle screw with contralateral translaminar facet screw fixation. The compared results will include the perioperative parameters (such as X-ray exposure, wound incision length, operative time, blood loss); screw angles of α1, β1, γ1, δ1 and ε1; postoperative complications; the VAS of back and leg pain; and the ODI.

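### The χ² test does not suit the number of X-ray exposures per patient, and for screw breaches it is valid only if the patient, not the screw, is the unit, which the protocol does not state

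*Protocol article*

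**What the plan says.** The Statistical analysis section gives one test to two outcomes: "The times of X-ray exposure and frequency of screw penetration out of the cortex will be compared using the" χ² test. It names neither a categorisation for the exposures nor a unit for the breaches.

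On exposures, the Primary outcomes section lists: "Wound incision length, operative time, intraoperative blood loss, times of X-ray exposure and complications". Table 1 records X-ray exposure once, on the day of surgery. The Discussion groups it with other measured quantities, "perioperative parameters (such as X-ray exposure, wound incision length, operative time, blood loss", and the Statistical analysis section gives those other three a two-sample t-test.

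On breaches, eligibility is limited to "Single-segment lower lumbar vertebral disease". The Study procedure section plans "two vertebral pedicle screws trajectories and one contralateral translaminar facet screw trajectory" for each patient, which makes three screws. The text after Figure 5 grades the screw rather than the patient: "The placement and position of the screws will be divided into three types (type I, the screw does not penetrate out of the cortex", followed by two grades of penetration. Screw position is also listed as a primary outcome.

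**The concern.** A χ² test compares the distribution of independent units over categories. The number of exposures in an operation is a count. If the word times is read as a duration, it is a continuous measure. Neither is categorical without a cut-point, and none is given. Fluoroscopy exposure matters to the trial's rationale, because the Introduction names radiation to patients and surgeons as a drawback of multiple X-ray guidance. The result should therefore include an estimate of how many exposures are avoided, and a χ² test does not give one.

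The three screws in one patient share one anatomy and one operation and, in the experimental arm, an individually designed template. If all screws go into a 2 × 2 table as independent observations, any positive correlation between them makes the standard error too small. The error then favours declaring a difference on a primary outcome.

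**Working it through.** **Number of patients.** The Sample size calculation uses 84.6% and 95%, power 0.8 and α 0.05. The pooled two-sided formula without continuity correction is

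n = [1.960·√(2·0.898·0.102) + 0.842·√(0.846·0.154 + 0.95·0.05)]² / 0.104² = (0.839 + 0.355)² / 0.010816 ≈ 131.8, so 132 per arm.

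The stated 132 is reproduced as a number per arm. The text does not say whether it is per arm or a total, so both 66 and 132 per arm are used below where it matters.

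**X-ray exposures, use 1: a table of distinct count values by arm.** The documents give no exposure counts, so the means are assumptions. Simulated Poisson counts, two-sided 5% level:

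| Assumed means | χ², 66 per arm | Wilcoxon, 66 per arm | χ², 132 per arm | Wilcoxon, 132 per arm |
|---|---|---|---|---|
| 10 vs 8.5 | 21% | 76% | 58% | 97% |
| 10 vs 8 | 46–50% | 95% | 91% | about 100% |
| 10 vs 7 | 95% | about 100% | 100% | about 100% |
| 10 vs 5 | 100% | about 100% | 100% | about 100% |

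The range in the second row comes from separate runs. Repeating the first row with 3,000 trials gave 23% against 79%, and 59% against 98%. With no true difference, this χ² test rejected in about 2–3% of trials, so it is conservative. With overdispersed counts (mean 10, SD 5; mean 20, SD 8 or 10), 66 per arm and a true 20% reduction, χ² power was 5–11%, against 64–84% for Wilcoxon and 69–86% for a t-test.

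**X-ray exposures, use 2: total exposures per arm.** The statistic (S₁ − S₂)²/(S₁ + S₂) assumes that the variance equals the mean. With φ = SD²/mean, the true type I error is about 2·[1 − Φ(1.96/√φ)]:

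- Poisson, φ = 1: 5% (simulated 4–5%).
- Mean 10, SD 5, φ = 25/10 = 2.5: 21.5% (simulated 21%).
- Mean 20, SD 8, φ = 64/20 = 3.2: 27% (simulated 27%).
- Mean 20, SD 10, φ = 100/20 = 5: 38% (simulated 39%).

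**Screw breaches, if the screw is the unit.** There are m = 3 screws per patient. The design effect is DE = 1 + (m − 1)·ICC = 1 + 2·ICC, and the true type I error of the nominal 5% test is 2·[1 − Φ(1.96/√DE)]. The ICC (within-patient correlation) is not in the documents.

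| Assumed ICC | DE | True type I error | Independent screws that 198 screws (66 patients) are worth |
|---|---|---|---|
| 0.02 | 1.04 | 5.5% | 190 |
| 0.05 | 1.1 | 6.2% | 180 |
| 0.1 | 1.2 | 7.4% | 165 |
| 0.2 | 1.4 | 9.8% | 141 |
| 0.3 | 1.6 | 12.1% | 124 |
| 0.5 | 2.0 | 16.6% | 99 |

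Beta-binomial simulation with an assumed 10% breach rate agrees: 6.9%, 12.0% and 16.6% at ICC 0.1, 0.3 and 0.5 with 66 patients per arm, and 7.5%, 11.9% and 16.5% with 132. The inflation depends on the design effect and hardly on the number of patients, so a larger trial does not remove it.

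**Screw breaches, if the patient is the unit.** Each patient contributes one yes/no result, patients are independent, and the χ² test keeps its nominal level.

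**The case against.** The strongest objection concerns the breaches. The protocol does not say that screws will be counted as independent. It gives no denominator for the frequency, and grading each screw describes data collection, not the unit of analysis. A χ² test on patients with any breach would be valid, and a condensed article may leave the unit to a fuller document. This stands, and it makes the breach part conditional. Still, the per-screw reading is the natural one, since the wording speaks of the frequency of screw penetration and nothing mentions a patient-level outcome.

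The size is also uncertain. Two pedicle screws in different vertebrae and one translaminar screw on another kind of path may be only weakly correlated, and at an ICC of 0.02 the type I error is about 5.5%. A reader might infer that the breach comparison has an inflated false-positive rate as a matter of fact. The documents do not support that, because they state neither the unit nor a correlation.

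On exposures, a template may reduce fluoroscopy by far more than 15%, and from 10 to 7 even the inefficient χ² test has about 95% power. That stands too, so it should not be inferred that the trial would miss a real reduction. It does not rescue the choice of test, because there is still no estimate of the difference and no defined table to test.

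Two further inferences go too far. The Sample size calculation does not name the event behind 84.6% and 95%, so the trial cannot be said to be sized on breaches. Nor are fewer X-rays and fewer breaches stated as the main benefits: the Abstract speaks of surgical accuracy and success rate, and its list of primary outcomes omits X-ray exposure, although the Primary outcomes section includes it.

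**Conclusion.** The exposure part holds with high confidence. The protocol actively assigns a categorical test to a per-patient quantity that it lists as primary, with no categories. One way of applying the test loses power, from 76% to about 21% in the least favourable Poisson case shown and by less as the true reduction grows. The other is anti-conservative under overdispersion, at about 21% to 39% for the spreads assumed. Neither estimates the difference. All these figures rest on assumed means and spreads.

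The breach part holds with moderate confidence and conditionally. If the screw is the unit, the plain χ² test ignores clustering of three screws per patient, and its true type I error is about 6% to 17% for an assumed ICC of 0.05 to 0.5. If the patient is the unit, the test is sound and only the statement of the unit is missing.

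**What to change.** Replace the sentence in the Statistical analysis section with two rules:

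- **X-ray exposures.** Compare the number per patient between arms by the Wilcoxon rank-sum test or by negative binomial regression, and report the difference or the rate ratio with a 95% confidence interval. If a duration is meant, say so; the rank test still applies.
- **Screw penetration.** Define a breach as type II or III against type I, and name the unit. Either compare the proportion of patients with any breach by χ² test, or analyse each screw by logistic GEE clustered on patient.

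In the Sample size calculation, state which event and which unit (screw or patient) the 84.6% and 95% refer to, so that the sizing and the analysis use the same unit.

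The cost is small. Exposure counts and screw grades are already collected, so no new data are needed. The per-screw comparison will have slightly wider intervals: by a factor of √1.1 ≈ 1.05 at ICC 0.05 and √2 ≈ 1.41 at ICC 0.5, the top of the assumed range. The choice should be fixed before the data are analysed, so that test and unit are not picked after seeing results.

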## Discussion

Translaminar facet screw fixation has been reported as a minimally invasive technique,^11 12 23^ and biomechanical comparisons between facet screw and pedicle screw fixation have revealed biomechanical equivalence between them.^14 15 24^ Unilateral lumbar pedicle screw may be used by some surgeons; however, Sethi *et al*^25^ used in vitro human cadaveric lumbar spines to compare the biomechanical properties of bilateral pedicle screws, unilateral pedicle screws (UPSs), UPSs and translaminar facet screws, and unilateral single pedicle screws and translaminar facet screws (V construct). They found that the UPS construct was the least stable in all loading modes and that the added translaminar facet screw enhanced the stability and stiffness. Similar results were obtained from a finite element analysis study.^26^ The biomechanical study of Luo *et al*^27^ revealed that a significantly larger displacement of the contralateral articular process was recorded in a model with only unilateral pedicle screws, and they reported that the unilateral pedicle screw combined with a contralateral translaminar facet screw had an instant and long-term equivalent biomechanical ability to that of the traditional bilateral pedicle screw (making it an alternative to the bilateral pedicle screw) and could be less invasive while maintaining stable and effective instrumentation.

Current computer-assisted surgery systems can achieve the accurate screw trajectory; however, the cost of computer-assisted surgery systems is considerable, and the manipulation is too complicated,^28^ whereas the accuracy remains dependent on multiple radiations.

Combining 3D reconstruction and 3D rapid printing is a new mode of production, which is applied in many fields because of the advantages of visualisation, plasticity and rapid printing.^29–31^ Moreover, 3D printing templates can help surgeons to achieve accurate screw placement for posterior cervical fixation and scoliosis.^32 33^

In this study, we will compare the 3D navigation template to multiple X-ray fluoroscopy for guiding a unilateral lumbar pedicle screw with contralateral translaminar facet screw fixation. The compared results will include the perioperative parameters (such as X-ray exposure, wound incision length, operative time, blood loss); screw angles of α1, β1, γ1, δ1 and ε1; postoperative complications; the VAS of back and leg pain; and the ODI.

The main strength of the study is the design as an RCT rather than an observational comparative study. An RCT has the advantage of controlling all possible variables due to the random sequence generation as opposed to observational studies, where confounding and bias may be more problematic. High-quality RCTs are generally regarded as the gold standard for studying the effectiveness of an intervention.

Because of some patients’ death, relocation or other reasons, the representativeness of the sample is destroyed. Meanwhile, if some patients accept experimental treatment measures such as therapeutic drugs, the results will appear to be deviated. For these experiment biases, strict monitoring can reduce the loss of follow-up and can also improve patient compliance, through which bias will decrease.

## Ethics and dissemination

The study had been reviewed and approved by the institutional ethics review board of the Second Affiliated Hospital and Yuying Children’s Hospital of Wenzhou Medical University. The procedure will be performed following the principles described in the Declaration of Helsinki. All of the participants will sign their informed consent. The protocol has been registered in the ChiCTR, assigned to be the representative registry of China to join the WHO ICTRP in 2007, with protocol number ChiCTR-IDR-17010466.

We will share individual patient data within 2 years after the trial is completed, and the original data will be collected using a clinical recording formula (both paper and electronic versions). The results will be presented at scientific communities (such as the International Congress of the Chinese Orthopaedic Association) and peer-reviewed journals.
